#### Case vignettes and assessment of PAD

It is essential that the persons taking part in the study fully understand what is meant by PAD and this cannot be taken for granted when addressing the general population. Physician-assisted dying is therefore explained in lay terms before the questions concerning PAD are posed.

For the vignettes, three cases were created: one about a person suffering from a non-terminal somatic illness, one about a person suffering from a terminal somatic illness, and one about a person suffering from a non-terminal mental illness. For each of these cases, there will be 16 different versions. Common to all of them will be the three factors of well-consideration, self-determination, and permanence of the desire to die. In contrast, the factors tolerability vs. intolerability of suffering, DMC vs. incapacity, the absence vs. presence of a therapeutic option, and the gender of the person depicted differ and are permuted with each other in the vignettes. This will result in a total of 48 different case vignettes. Expert ratings will be used to assess the interrater reliability of the case vignettes. To ensure that the assessment of different raters has a concurrent outcome, interrater reliability is calculated using Fleiss' kappa with a target value of at least 0.8, indicating substantial agreement (22). This measure has the advantage over other kappas such as Cohen's kappa that interrater reliability by more than two raters can be tested.

Each participant will be randomly assigned three case vignettes—one (out of 16 possible variations) about a person suffering from a non-terminal somatic illness, one (out of 16 possible variations) about a person suffering from a terminal somatic illness, and one (out of 16 possible variations) about a person suffering from a non-terminal mental illness. For these three concrete situations, the participant will be asked to assess whether physician-assisted suicide should be granted or not. The participant will define the degree of his or her approval or disapproval on a 5-point Likert scale and will be asked to justify the decision by describing his or her motives in an open answer format. Furthermore, participants will be asked to select those items from a list of alternative justifications that are decisive for their judgment.

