### Statistical analysis

The primary endpoint will be the degree of consent to PAD depending on the type of illness (somatic vs. mental).

In addition, the following secondary endpoints have been defined:

1. Degree of consent to PAD as a function ofa. the intolerable sufferingb. DMCc. the availability of therapeutic optionsd. the terminal nature of the illness.2. Positioning of the respondents to the SAMS criteria of 2004, 2018, and 2021.a. Spontaneously expressed opinions in an open answer format in the context of a qualitative evaluation.b. Agreement or disagreement when presented SAMS criteria of 2004, 2018, and 2021.3. Association between the positioning of the respondents on the SAMS criteria of 2004, 2018, and 2021, and the evaluation of the case vignettes.4. Association between the degree of stigmatization and the assessment of PAD.5. Comparison of the primary and secondary endpoints between the two groups.

The statistical analysis of the collected data will be done with a standard statistical package, either IBM SPSS Statistics (IBM Corp, released 2020, IBM SPSS Statistics for Windows, Version 27.0, Armonk, NY: IBM Corp.) or R Studio (RStudio Team, released 2020, RStudio: Integrated Development for R. Boston, MA: RStudio, PBC). The descriptive statistics of the sample characteristics will be performed separately for the two groups and the whole sample. For binary and categorical variables, we will report frequencies in numbers and percentages; for continuous variables, we will report the mean and standard deviation, and the median and interquartile range, respectively. Given the fact that our research project is an exploratory study, we do not explicitly specify significance levels. The primary endpoint [level of PAD consent as a function of the type of illness (somatic vs. mental)] will be evaluated in a simple regression analysis with the level of PAD consent as the dependent variable and type of illness as the independent variable. In a multiple regression analysis, we will further examine the association of demographic factors such as gender with the dependent variable. The variables general population/medical professional and gender will be controlled for statistically whenever necessary. The secondary endpoints will be evaluated—as far as possible—with the same analyses. To explore the responses from the free-text fields, computer-assisted content analysis will be used (MAXQDA12; VERBI Software GmbH, Berlin, Germany).

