We will test for differences between the two groups using two-tailed *t*-tests (in the presence of a normal distribution) or the Mann-Whitney U test (in the absence of a normal distribution) for continuous variables and the Chi^2^-test for categorical variables.

The model assumption will be checked in advance and the distributions of the endpoints will be plotted with scatter plots. If any model assumptions are not met, confidence intervals will be created using bootstrap. This resampling-based, non-parametric procedure can also be used if the model's normal distribution assumptions are not met.

If a participant completes the online survey entirely, missing values are not to be expected, as the survey will be designed in a manner such that it can only be completed if all fields are filled in. Missing values in incomplete surveys can be considered “data missing at random” and estimated via multiple imputations. Outliers will be identified and checked for their plausibility. If a participant drops out of the online survey this will be registered and the dropout rates of both groups will be explored. By choosing an appropriately large sample size response dropouts have been accounted for.

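### The primary and multiple regressions ignore that each respondent supplies three ratings: the illness-type interval comes out too wide, and intervals for respondent-level predictors too narrow

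*Protocol article*

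**What the plan says.** Protocol article, Case vignettes and assessment of PAD: "Each participant will be randomly assigned three case vignettes", one each for a non-terminal somatic, a terminal somatic and a non-terminal mental illness. For each of the three, "The participant will define the degree of his or her approval or disapproval on a 5-point Likert scale". Suffering, decision-making capacity (DMC), therapeutic option and the depicted person's gender vary across the 16 versions of each case.

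Protocol article, Statistical analysis: the primary endpoint is consent by illness type, somatic against mental. It is to be "evaluated in a simple regression analysis with the level of PAD consent as the dependent variable and type of illness as the independent variable". The section continues: "In a multiple regression analysis, we will further examine the association of demographic factors such as gender with the dependent variable". It adds: "The variables general population/medical professional and gender will be controlled for statistically whenever necessary". On the rest: "The secondary endpoints will be evaluated—as far as possible—with the same analyses". The same section also plans two-group tests between physicians and the public.

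On failed assumptions it says: "If any model assumptions are not met, confidence intervals will be created using bootstrap". It does not say what is resampled. No random effect, GEE, clustered standard error or paired analysis is named.

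**The concern.** Every respondent rates both illness types, so illness type varies only within a person. It can serve as a predictor of consent only if each person contributes more than one row. Simple regression on such rows treats all of them as independent. A person's general attitude to assisted dying will very likely make the three ratings correlate.

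Ignoring that correlation has opposite effects on two kinds of predictor. For a contrast within persons, the analysis discards the gain from pairing and reports an interval that is too wide. For a characteristic of the person, it counts three ratings as three independent people and reports an interval that is too narrow. The second effect matters more here, because the study is meant to generate hypotheses, and associations with gender, profession or attitude to the guidelines would look firmer than the data allow.

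**Working it through.** **The plan's own figure.** The article gives precision only for a single proportion per group: 2,373 (public) and 2,258 (physicians) at 95% confidence and a 2% margin.
- Without a finite-population correction, n = 1.96² × 0.25 / 0.02² = 2,401. This is within 1.2% of 2,373 and 6.3% above 2,258.
- With the correction, the stated sizes imply populations of about 200,000 to 204,000 and about 38,000. The article gives neither, so these are back-calculated.
- No interval width or power is stated for the primary regression, so there is no such figure to reproduce.

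**Inputs.** From the article: three ratings per person (two somatic, one mental) and 3,000 expected respondents per group. Assumed: equal variance σ² and one common correlation ρ between a person's ratings, at 0.2 / 0.4 / 0.6.

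**Illness type (primary).** The estimate is the mental mean minus the mean of the two somatic ratings.
- Naive variance: σ²(1/n + 1/(2n)) = 1.5σ²/n.
- Correct variance: σ²[1 + (1 + ρ)/2 − 2ρ]/n = 1.5σ²(1 − ρ)/n.
- Correct/naive SE = √(1 − ρ) = 0.89 / 0.77 / 0.63. Inverted, the naive SE is 1.12 / 1.29 / 1.58 times the correct one.
- Coverage of the nominal 95% interval, 2Φ(1.96/ratio) − 1: 97.2% / 98.9% / 99.8%.
- Half-width with n = 3,000: naive 1.96 × √(1.5/3000) = 0.044 SD; correct 0.039 / 0.034 / 0.028 SD.

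**Respondent-level predictors, all ratings pooled.** The variance of a person's mean rating is σ²(1 + 2ρ)/3, against a naive σ²/3.
- Correct/naive SE = √(1 + 2ρ) = 1.18 / 1.34 / 1.48.
- Coverage: 90.2% / 85.6% / 81.4%.
- Physicians against public, 3,000 each: naive half-width 1.96 × √(2/9000) = 0.029 SD; correct 0.035 / 0.039 / 0.043 SD.

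**Simulation check.** Five-point ratings, 600 respondents, 1,500 runs, ρ as the correlation of the underlying latent scale.

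| Nominal 95% coverage, naive OLS | ρ = 0.2 | ρ = 0.4 | ρ = 0.6 |
|---|---|---|---|
| Illness type | 96.7% | 98.5% | 99.7% |
| Respondent-level predictor | 91.0% | 87.3% | 82.0% |
| Factor randomised per vignette | 94.2% | 94.6% | 94.4% |

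Respondent-clustered standard errors gave 94% to 96% throughout.

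**Bootstrap check.** One simulated data set, 1,000 respondents, 2,000 resamples, latent ρ = 0.5 (observed correlation 0.48).

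| SE | Illness type | Group |
|---|---|---|
| Naive OLS | 0.051 | 0.048 |
| Resampling single ratings | 0.050 | 0.047 |
| Resampling respondents | 0.039 | 0.065 |

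**Sensitivity to the common correlation.** If the two somatic ratings correlate at a and each correlates with the mental rating at b, the correct variance of the illness-type contrast is σ²(1.5 + 0.5a − 2b)/n. The naive interval is too wide whenever b exceeds a/4, a condition that any common positive correlation meets.

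**The case against.** A condensed article may leave modelling detail to a fuller plan. That would excuse silence, but the article names a specific model, and that model does not match the three-vignette design.

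The study is exploratory and sets no significance level. This lowers the stakes but does not remove the problem, because confidence intervals and tests are planned.

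Several limits stand in full:
- A reader might infer that the primary result is exposed to false positives, or that its interval is wrong in both directions. The design does not support that. With positive common correlation the primary error runs one way, towards caution, and the estimate is unbiased with complete triplets. The article expects complete records from finished online surveys.
- A reader might infer that the bootstrap resamples single ratings. The article does not say so. Resampling respondents would give valid intervals; the fault is that the unit is left open.
- Suffering, DMC and therapeutic option, if drawn separately for each vignette, are hardly affected.
- Stigma may be related only to the mental vignette, since the Primary objective section links it to acceptance of mentally ill persons' wishes. That analysis has one rating per person and no clustering. Research question 5 is worded more broadly, so the use is unclear. The physician/public tests escape in the same way if run separately for each vignette type.
- In absolute terms the differences are small: at most 0.016 SD for illness type (0.044 − 0.028) and 0.014 SD for group (0.043 − 0.029).

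**Conclusion.** The point holds in a limited form. The named regressions do not fit a design in which each person gives three ratings.

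For illness type, the cost is lost precision: an interval 1.12 to 1.58 times as wide as it should be, around an unbiased estimate. For gender, professional group, positioning on the guidelines, and stigma if all ratings are used, pooled analysis gives intervals with about 90% down to 81% coverage in place of 95%.

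These sizes rest on an assumed correlation of 0.2 to 0.6, equal for all pairs of ratings, which the article does not give. The respondent-level figures also assume that all three ratings are pooled.

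This is a should-fix matter. The primary interval is conservative, and the too-narrow intervals concern exploratory respondent-level associations.

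**What to change.** In the Statistical analysis section, replace the simple and multiple regressions of the vignette ratings with either:
- one model of all ratings with a respondent random intercept (linear or cumulative-logit mixed model); or
- GEE, or ordinary regression, with standard errors clustered on respondent.

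State that any bootstrap resamples respondents together with all their ratings. Say for the stigma analysis and the physician/public tests whether they use one vignette type or pool all three; if pooled, the same clustering applies. Report the estimated within-person correlation, so that the assumption used here can be checked.

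The cost is analysis wording only. Recruitment, questionnaire and sample size are unchanged, and both packages named in the article can fit these models.

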Using the online tool Random.org (https://www.random.org/sequences/), case vignettes will be randomized and assigned to participants via a randomly generated sequence based on the address lists.

Furthermore, we aim to assess participants' opinions on the SAMS ethical guidelines of 2004, 2018, and 2021. For this purpose, participants will be presented with the guidelines and will be asked to indicate their degree of agreement on the criteria using a 5-point Likert scale (1 = complete rejection, 5 = complete agreement).

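### Bootstrap intervals are the only stated remedy for any failed regression assumption, but they do not address non-linearity in secondary endpoints 3 and 4

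*Protocol article*

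**What the plan says.** All of the following is in the protocol article; the section is Statistical analysis unless another is named.

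- **Model.** The primary endpoint "will be evaluated in a simple regression analysis with the level of PAD consent as the dependent variable and type of illness as the independent" one. For the rest, "The secondary endpoints will be evaluated—as far as possible—with the same analyses".
- **Check.** "The model assumption will be checked in advance and the distributions of the endpoints will be plotted with scatter plots".
- **Remedy.** "If any model assumptions are not met, confidence intervals will be created using bootstrap". The next sentence adds: "This resampling-based, non-parametric procedure can also be used if the model's normal distribution assumptions are not met". Normality is the only assumption named. The rank test mentioned in the same section serves the comparison of the two groups, not the regressions.
- **Endpoints with graded predictors.** Endpoint 3 is "Association between the positioning of the respondents on the SAMS criteria of 2004, 2018, and 2021, and the evaluation of the case vignettes". Its predictor comes from respondents being "asked to indicate their degree of agreement on the criteria using a 5-point Likert scale (1 = complete rejection, 5 = complete agreement") (Case vignettes and assessment of PAD). Endpoint 4 is "Association between the degree of stigmatization and the assessment of PAD". Its predictors are social-distance items scored 1 to 4 and a coercion-attitude scale (Survey instruments).
- **Outcome.** Consent to PAD is itself rated on five points.

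**The concern.** The remedy is written for *any* failed assumption, but it suits only some of them. A bootstrap re-estimates the sampling variability of a coefficient. It does not change which coefficient is fitted. If the residuals are skewed or their variance is unequal, that is what is needed. If mean consent does not follow a straight line in the predictor, the bootstrap gives an interval for the same straight-line slope.

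Type of illness and the vignette factors are two-level, so a line through two means always fits and nothing is lost. Guideline agreement and the stigma scores are graded, so linearity is a real assumption for them. A U-shaped relation could then be read as little or no association. An effect confined to one end of the scale could be read as a gradient across everyone.

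The section Importance of the research question says that a link between prejudice and the assessment of wishes to die may point to a need for public or professional education. For that use, it matters whether the association runs across the scale or sits in a small group.

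**Working it through.** The plan gives no figure on this point. The only input taken from it is the expected number of records: 30% of 10,000 = 3,000 per group, or 6,000 for both (Sample characteristics). Everything else below is assumed.

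**Endpoint 3, set-up.** Agreement x takes the values 1 to 5 with probability 20% each. Consent is a latent mean f(x) plus normal error (SD 1), rounded and cut to 1-5. There is one rating per respondent and n = 3,000. The ordinary least-squares slope is fitted, with a percentile bootstrap of 1,000 case resamples. The four assumed shapes are:

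- U: f = 2.2 + 0.4(x - 3)²
- jump at level 5 only: f = 2.5, plus 1.5 at x = 5
- jump from level 1 to 2 only: f = 2.0, plus 1.5 for x ≥ 2
- linear: f = 3 + 0.3(x - 3)

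| Shape | Mean consent at x = 1, 2, 3, 4, 5 | Slope | Bootstrap 95% interval | Ordinary 95% interval |
|---|---|---|---|---|
| U | 3.71, 2.58, 2.28, 2.61, 3.78 | 0.017 | -0.012 to 0.046 | -0.012 to 0.046 |
| Jump at 5 | 2.52, 2.47, 2.58, 2.57, 3.97 | 0.302 | 0.275 to 0.329 | 0.276 to 0.328 |
| Jump 1 to 2 | 2.08, 3.50, 3.38, 3.53, 3.49 | 0.285 | 0.257 to 0.311 | 0.258 to 0.311 |
| Linear | 2.50, 2.70, 3.00, 3.27, 3.58 | 0.273 | 0.247 to 0.295 | 0.248 to 0.298 |

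**Hand check.** With equal shares the slope is Σ(x - 3)·mean(x) / Σ(x - 3)², and the denominator is 4 + 1 + 0 + 1 + 4 = 10.

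- U: (-2×3.71 - 2.58 + 2.61 + 2×3.78)/10 = 0.17/10 = 0.017
- Jump at 5: (-2×2.52 - 2.47 + 2.57 + 2×3.97)/10 = 3.00/10 = 0.300
- Jump 1 to 2: (-2×2.08 - 3.50 + 3.53 + 2×3.49)/10 = 2.85/10 = 0.285
- Linear: (-2×2.50 - 2.70 + 3.27 + 2×3.58)/10 = 2.73/10 = 0.273

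These match the fitted slopes to within 0.002. The slope is one weighted contrast of the five means. It is near zero for the U although the means differ by up to 3.78 - 2.28 = 1.50 points. It is about 0.3 for two different jumps and for a true gradient alike.

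**Larger sample.** At n = 6,000 the U gives 0.002 (-0.020 to 0.023) and the jump at 5 gives 0.276 (0.256 to 0.295). More data narrow the interval but do not reveal the shape.

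**Endpoint 4.** The stigma score is drawn from a normal distribution (mean 2.6, SD 0.6) cut to 1-4, with n = 3,000.

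- U shape, f = 2.2 + 1.2(s - 2.6)²: slope -0.04 (-0.12 to 0.04). Band means, with cuts at 1.5, 2, 2.5, 3 and 3.5, are 4.13, 2.99, 2.39, 2.24, 2.71 and 3.61.
- Jump of 1.5 above a score of 3.2: slope 0.51 (0.44 to 0.58). Mean consent is flat at 2.47 to 2.57 in the four bands below 3.

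A second illustration uses a standardised predictor z and latent SD 1.2. A fall in latent consent of 0.9, confined to z > 1.04 (about the top 15% of a standard normal), gives a slope of -0.18 per SD (-0.22 to -0.14). The slope below the threshold is 0.01.

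**Where the remedy works.** With a linear mean and skewed errors of unequal variance (n = 1,000, 200 repeats), the bootstrap interval covered the true slope in 97% of repeats.

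**The case against.** The case on the other side is substantial, and most of it limits the point without removing it.

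- **The text leaves latitude.** The remedy sentence says how intervals are made; it does not say that the model stays fixed. Secondary endpoints follow the primary analysis only as far as possible. The article never writes the word linear, although regression with normality assumptions on a five-point score implies it. A fuller plan may code these predictors as categories. This stands as mitigation, but the printed rule would still need narrowing, because it offers the bootstrap for any failure.
- **The follow-on sentence may only explain the choice.** It need not extend the rule beyond normality. That is fair, but the rule's own wording already covers every assumption.
- **A reader might infer that the slopes will be wrong and their intervals falsely tight.** The documents do not support that. The slope remains the best straight-line summary and its interval is valid for that quantity. In the guideline-agreement cases the bootstrap and ordinary intervals agree to within 0.003, so the bootstrap adds no false precision. In the threshold cases the slope does detect that an association exists, which is what endpoints 3 and 4 ask for.
- **A reader might extend the point to age.** Age is collected, but the multiple regression names only gender as an example of a demographic factor, so the text does not establish it.
- **Nothing in the documents suggests a curve or a threshold.** The symmetric U is the worst case for a slope. Assumptions are to be checked in advance and the work is exploratory, without significance levels. This stands in full and sets the weight of the point.

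**Conclusion.** The point holds as a minor one. The stated remedy does not match one of the assumptions it claims to cover. The mismatch bears on secondary endpoints 3 and 4 only; the primary endpoint and endpoint 1 are untouched.

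If linearity failed there, one slope could be an incomplete or misleading description, ranging from near zero under a U shape to a gradient-like 0.3 per scale point under a single jump. Those sizes rest on assumed shapes, assumed error SDs and one rating per respondent. In the study each respondent rates three vignettes, and that dependence is a separate matter. The documents neither show nor exclude non-linearity, so no bias in the eventual results can be claimed. No sample-size figure changes.

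**What to change.** Narrow the remedy sentence and add one for linearity, for example:

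> Bootstrap intervals will be used where residuals are non-normal or their variance is unequal. Where the check shows a non-linear relation with a graded predictor, guideline agreement will be entered as five categories and stigma scores as categories or a spline, and mean or predicted consent will be reported across the predictor's range.

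The cost is one or two sentences and a few more model runs on data already planned. Five categories use four parameters in place of one slope, which is three more per guideline item and negligible at about 3,000 records per group. The benefit is that the reported shape, not just one slope, can inform any conclusion about stigma and education.

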### Sample characteristics

For this study, we will survey a group of 10,000 Swiss residents from the general population including the three language regions (German, Italian, and French) as well as a group of 10,000 physicians practicing in the states (“cantons”) of Basel-Stadt, Basel-Landschaft, Aargau, Lucerne, Graubünden, Ticino, and Vaud. In total, the sample thus comprises 20,000 individuals. For each of the two groups, we performed a case number estimation to determine the size of a significant sample. For the group from the general population, our case number estimation showed that a sample size of *n* = 2,373 yields significant results at a 95% confidence interval and a margin of error of 2%. Based on the literature and our empirical values, we assume a response rate of 30%, which corresponds to 3,000 valid records for 10,000 persons and thus harmonizes with our estimated representative sample size. We also performed a case number estimation for the group of medical professionals, which indicated a sample size of *n* = 2,258 as significant at a 95% confidence interval and a margin of error of 2%. According to the 2019 FMH statistics, we plan to survey 10,000 physicians. Therefore, with a response rate of 30%, we can expect 3,000 valid data sets.

Eight thousand residents from the state of Basel-Stadt are to be randomly drawn from the state's register and contacted via postal mail. Furthermore, a sample of 2,000 individuals of the general population from the Italian- and French-speaking parts of Switzerland will be recruited by a polling institute. For the survey of the 10,000 physicians from Basel-Stadt, Basel-Landschaft, Aargau, Lucerne, Graubünden, Ticino, and Vaud we rely on the cooperation with the responsible health departments.

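### A large sample is said to account for dropouts, but with 70% expected non-response it protects only precision, and break-off is declared missing at random without a condition

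*Protocol article*

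**What the plan says.** Two sections of the protocol article bear on this.

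- **Sample characteristics.** The targets are 2,373 (general population) and 2,258 (physicians), each from a 95% confidence interval with a 2% margin of error. For the public, "we assume a response rate of 30%, which corresponds to 3,000 valid records for 10,000 persons", and the text says this fits a sample size that it calls representative. For physicians, "with a response rate of 30%, we can expect 3,000 valid data sets".
- **Statistical analysis.** All fields must be filled in before the survey can be completed, so missing values arise from break-off. "Missing values in incomplete surveys can be considered “data missing at random” and estimated via multiple imputations". Then: "If a participant drops out of the online survey this will be registered and the dropout rates of both groups will be explored". The paragraph closes: "By choosing an appropriately large sample size response dropouts have been accounted for".

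Under Case vignettes and assessment of PAD, each participant is randomly assigned one version of each of three cases, rates all three on a 5-point scale and justifies each rating in free text.

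**The concern.** Two losses are involved and should be kept apart.

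**Never responding.** Seven in ten people contacted are expected not to take part. Contacting 10,000 to obtain 3,000 restores the count. It does not make the 3,000 resemble the 7,000. If willingness to answer goes with opinion on assisted dying, reported acceptance is shifted, and the narrow interval then hides the shift.

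**Breaking off.** Among those who start, missing at random is asserted without a reason or a condition. A person may stop because of the vignette drawn, or rather than state the opinion that would then be imputed. The only check named splits dropout by public versus physicians, which shows neither mechanism.

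At stake are the acceptance levels in each group, the public/physician comparison and, through break-off, the contrasts between randomised vignette versions.

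**Working it through.** **1. The plan's own figures.** For one proportion at p = 0.5, n0 = 1.96² × 0.25 / 0.02² = 2,401. The stated 2,373 is 1.2% below this. With the finite-population correction n = n0 / (1 + (n0 − 1)/N), 2,373 corresponds to N of about 204,000 and 2,258 to N of about 37,900. The article does not state these N; they are back-solved. The basis is sampling error alone.

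**2. The count is covered.** 10,000 × 0.30 = 3,000 per group. Room for further loss is 1 − 2,373/3,000 = 20.9% and 1 − 2,258/3,000 = 24.7%. The random margin at 3,000 is 1.96 × √(0.25/3,000) = 1.79 points.

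**3. Non-response bias in a level.** Bias = (1 − response rate) × (responder mean − non-responder mean) = 0.7 × d. Sample size does not appear. The article gives no d, so these values are assumptions:

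| d (points) | Bias (points) |
|---|---|
| 2 | 1.4 |
| 2.9 | 2.0 (the whole planned margin; 2/0.7 = 2.86) |
| 5 | 3.5 |
| 10 | 7.0 |

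True coverage of the nominal 95% interval at p = 0.5:

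| d | n = 2,373 | n = 3,000 | n = 30,000 |
|---|---|---|---|
| 2 | 72% | 66% | 0.2% |
| 5 | 7% | 3% | about 0% |

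A larger sample makes coverage worse, because the interval narrows around the wrong value.

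**4. Contrasts.** With 30% response in both groups, the bias in public minus physicians is 0.7 × (d in public − d in physicians). For the primary contrast, each person rates somatic and mental cases, so a uniform shift in attitude cancels. The bias is 0.7 × (illness-type effect in responders − effect in non-responders).

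**5. Break-off.** An illustrative simulation used assumed 5-point ratings, about 20% break-off at the mental-illness vignette and a true mental-minus-somatic difference of −0.825. Imputation was represented by its regression point estimate. Bias in that difference:

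| Break-off depends on | Complete cases | Imputation without vignette version | Imputation with version |
|---|---|---|---|
| Assigned version (30% vs 10%) | +0.046 | +0.045 | 0.000 |
| Unseen rating (40% at 1, 25% at 2, 10% above) | +0.083 | +0.118 | +0.103 |

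The results were the same to within 0.001 at n = 3,000, 30,000 and 300,000.

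**The case against.** The closing sentence follows text about people who leave the online survey, and its natural reading concerns numbers. On numbers it is right (step 2). The study is declared exploratory, dropout will be registered and explored by group, and the content of an imputation model is commonly left to an analysis plan that is not shown. The word representative qualifies a sample size and does not say outright that responders mirror non-responders.

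Much of this stands. The absence of a detailed imputation model is not an error in itself. What remains is that the sentence says dropouts are accounted for without restricting this to precision, that a count is linked to representativeness, and that missing at random is stated unconditionally. A fuller analysis plan would not make those statements correct.

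Three stronger readings are tempting but not supported:

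- *Vignette-dependent break-off refutes missing at random.* It does not. The assignment is randomised and known, and imputation that includes it removes that bias (step 5). Only dependence on the unstated opinion breaks the assumption. That is plausible for this topic, but nothing in the article shows it.
- *Non-response of 70% undermines the primary result.* A general attitude shift cancels within person, so this needs the illness-type effect itself to differ by response status.
- *The missing-at-random sentence covers the 70%.* It covers incomplete surveys only.

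That people with strong views respond more often is likewise an assumption.

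**Conclusion.** The point holds in limited form. Sample size accounts for lost precision and for nothing else. Bias in acceptance levels is 0.7 times the responder/non-responder difference, which reaches the planned 2-point margin once that difference is about 2.9 points. The public/physician comparison is biased to the extent that the difference is unequal in the two groups. These figures rest on the plan's 30% response rate and on assumed differences. They show what the sample size cannot exclude and do not estimate the actual bias.

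The primary somatic/mental contrast is partly protected by the within-person design. For break-off, the missing-at-random statement needs a condition (vignette assignment in the imputation model) and a sensitivity analysis for the part that no imputation under that assumption can repair. The simulated biases are illustrations under assumed break-off rates. For an exploratory survey this calls for corrected wording and a few added analyses, not a redesign.

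**What to change.** 1. In Statistical analysis, limit the closing sentence to precision. In Sample characteristics, drop the word representative.
2. Weight responders to frame totals by age and gender where a frame exists, or at least compare them with it: the Basel-Stadt register, and the physician lists if totals can be obtained. Report acceptance levels weighted and unweighted. Both variables are already collected and only totals are needed, so anonymity is kept. No frame is described for the 2,000 people recruited by the polling institute. Weighting physicians by canton is not available as planned, since canton is not among the listed questionnaire items.
3. Tabulate break-off by assigned case and factor level as well as by group.
4. Include the vignette factors and earlier answers in the imputation model.
5. Add one delta-shifted imputation as a sensitivity analysis. Replacing imputation by a likelihood model on all completed ratings would not serve this purpose, because it rests on the same missing-at-random assumption.

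The cost is a request for frame totals, a few tables and slightly wider weighted intervals. Data collection is unchanged. Weighting removes only the bias explained by age and gender, so the report should still say that opinion-driven non-response cannot be excluded.
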